## Abstract

**Background:**

Cosmetic result following breast conserving surgery (BCS) for cancer influences quality of life and psychosocial functioning in breast cancer patients. A preoperative prediction of expected cosmetic result following BCS is not (yet) standard clinical practice and therefore the choice for either mastectomy or BCS is still subjective. Recently, we showed that tumour volume to breast volume ratio as well as tumour location in the breast are independent predictors of superior cosmetic result following BCS. Implementation of a prediction model including both factors, has not been studied in a prospective manner. This study aims to improve cosmetic outcome by implementation of a prediction model in the treatment decision making for breast cancer patients opting for BCS.

**Methods/design:**

Multicentre, single-blinded, randomized controlled trial comparing standard preoperative work-up to a preoperative work-up with addition of the prediction model. Tumour volume to breast volume ratio and tumour location in the breast will be used to predict cosmetic outcome in invasive breast cancer patients opting for BCS. Three dimensional (3D)-ultrasonography will be used to measure the tumour volume to breast volume ratio needed for the prediction model. Sample size was estimated based on a 14% improvement in incidence of superior cosmetic result one year after BCS (71% in the control group versus 85% in the intervention group). Primarily cosmetic outcome will be evaluated by a 6-member independent panel. Secondary endpoints include; (1) patient reported outcome measured by BREAST-Q, EORTC-QLQ-C30/BR23 and EQ-5D-5 L (2) cosmetic outcome as assessed through the BCCT.core software, (3) radiation-induced reaction (4) surgical treatment performed, (5) pathological result and (6) cost-effectiveness. Follow-up data will be collected for 3 years after surgery or finishing radiotherapy.

**Discussion:**

This randomized controlled trial examines the value of a preoperative prediction model for the treatment-decision making. It aims for a superior cosmetic result in breast cancer patients opting for BCS. We expect improvement of patients’ quality of life and psychosocial functioning in a cost-effective way.

**Trial registration:**

Prospectively registered, February 17th 2015, at ‘Nederlands Trialregister - NTR4997’.

**Electronic supplementary material:**

The online version of this article (doi:10.1186/s12885-017-3280-y) contains supplementary material, which is available to authorized users.

## Background

For early stage breast cancer patients the goal of therapy is to ensure both local control and breast preservation with an optimal cosmetic outcome. The current standard of care is breast-conserving surgery (BCS) followed by adjuvant whole breast irradiation [1–3]. Large randomised clinical trials in the 80’s have shown that this treatment is equivalent, in terms of overall and breast-cancer specific survival, to a mastectomy [4]. The frequency of BCS performed is estimated at an annual rate of 60% in the Netherlands [5]. Oncoplastic surgery, an operation performed jointly by a plastic surgeon and a breast-cancer surgeon specialist, is currently more frequently performed with the goal of obtaining the best cosmetic outcome possible. At time of diagnosis, however, the treatment decision whether to perform a mastectomy (with or without a breast reconstruction) or BCS is often subjective. Unfavourable cosmetic outcome following BCS is significantly associated with decreased quality of life and psychosocial functioning [6, 7]. Poor cosmetic outcome following BCS is reported in up to 30% of breast cancer patients [8–11]. Pre-operative knowledge of the expected cosmetic outcome would thus be a welcome treatment decision aid.

As previously studied by our group, independent factors for the prediction of cosmetic outcome in BCS are tumour location and tumour volume to breast volume ratio. This volume ratio was obtained through 3-D visualisation of breast MRI images (10). Based on these factors a prediction model is made predicting the expected cosmetic outcome for BCS. The prediction model could aid in the treatment decision by differentiation of patients with an expected favourable cosmetic outcome and thereby improve cosmetic outcome and patients’ quality of life.

Within this randomised trial participant will undergo an additional 3-D ultrasonography of the affected breast. Ultrasonography has a broad clinical applicability in breast cancer patients and is not dependent on the use of ionizing radiation. Measurements, obtained by the Automated Breast Volume Scanner (ABVS) and 3-D ultrasonography (3-D US) have previously been compared to MRI and histopathological tumour size with good agreement [12, 13]. An additional validation compared volume measurements of the3-D US to those measured by histopathological and 3-D MRI. Both breast and tumour volume showed high agreement (unpublished data).

This study aims to improve cosmetic outcome following BCS by using a preoperative prediction model based on 3-D ultrasonography.

### Objective

The objective of this randomized controlled trial is to compare cosmetic outcome following a standard preoperative work-up by that of the preoperative prediction model. The hypothesis is that the addition of the preoperative prediction model aids in the treatment-decision making and therefore improves cosmetic outcome and quality of life in patients opting for BCS.

## Methods/design

### Trial design

This single-blinded, multicentre, randomised controlled trial targets women with the diagnosis of primary breast cancer. Patients will randomly be assigned (1:1) to either the intervention or control group after written informed consent is given. The study is in compliance with the Helsinki declaration. Ethical approval has been granted by the Institutional Review Board of the Erasmus University Medical Centre, Rotterdam, the Netherlands (reference-number: MEC-2013-360). This trial is registered before the start of the inclusion on February 17th, 2015 (NTR 4997). Figure 1 present a flow-diagram of the trial design.

**Fig. 1 Fig1:**
[figure not shown]
Flow chart TURACOS trial

### Participants

Women with pathologically confirmed primary invasive breast cancer (cT1–3) that are eligible and opt for BCS will be included. Additional inclusion and exclusion criteria are presented in Table 1.

**Table 1 Tab1:** Inclusion and exclusion criteria

Inclusion criteria	Exclusion criteria
Female	Recurrent breast cancer ipsilateral
Aged >18 years	Previous radiation therapy ipsilateral breast
Primary breast cancer	
Pathologically proven breast cancer TI-III	
Eligible for breast conserving surgery (BCS)	

### Interventions

#### Volumetric measurements

All patients will receive an additional ultrasound performed by the Automated Breast Volume Scanner (ABVS– ACUSON S2000™ ABVS, Siemens Medical Solutions, Inc., Mountain View, CA) available at the department of Radiology, Erasmus MC Cancer Institute [14]. A standardized scanning technique is used where 3 or 5 scans are performed (i.e. anterior-posterior, lateral and medial view or anterior-posterior, upper lateral-, lower lateral-, upper medial- and lower medial-quadrant). Data from the ABVS is visualised by the ‘V-scope’ software (department of Bioinformatics, Erasmus MC) through an interactive 3-D image on the desktop system. Volume measurements are performed using a tracking system and a wireless joystick [15].

#### Prediction model

The tumour to breast volume ratio and the location of the tumour in the breast are used in the prediction model to calculate the chance of superior cosmesis in case of BCS. If the probability exceeds the predefined threshold primary BCS is advised. If the probability is below the predefined threshold an alternative treatment will be advised (i.e. oncoplastic BCS, mastectomy with or without a breast reconstruction or neo-adjuvant chemotherapy). The threshold is defined by modelling the differences in quality of life utilities between the different surgical strategies and the associated cosmetic results.

#### Pre-operative work-up

For all randomized patients the following characteristics will be collected (if applicable): age, body mass index (BMI), comorbidity, previous operations, smoking status, hormonal status, tumour morphology, TNM stadium, post-operative complications, radiotherapy details, chemotherapy details and hormonal therapy details.

Preoperatively all patients will be asked to complete three questionnaires. This includes the ‘Breast Q – preoperative modules’ [16], the ‘European Organisation of research and Treatment of Cancer quality of life questionnaire (EORTC-QLQ-C30 version 3 and EORTC-QLQ-B23 version 1)’ and ‘Euro-QoL 5D-5 L questionnaire’ (EQ-5D-5 L-version 2). All patients will preoperatively be discussed in multidisciplinary consultation. For the intervention group, the optimal treatment based on the results of the prediction model will be taken into consideration. All patients will be blinded for the result of the prediction model. Preoperative photographs will be taken by a professional medical photographer. These photographs include the 1) face-view position with the arms down, 2) face-view with arms in the side and 3) lateral view (90°) off the affected breast. The face view photographs will cover the area of chin to the umbilicus protecting the subject’s privacy and anonymity.

#### Follow-up

Three questionnaires will be obtained at all follow-up visits (i.e. ‘BREAST-Q postoperative modules’, the EORTC-QLQ-C30/B23 and the EQ-5D-5 L. Follow-up visits will be scheduled at 3 months (T1), 1 year (T2), and 3 year (T3) postoperatively. Photographs will be obtained both 1 and 3 year following BCS.

### Outcomes

The outcome measures are summarized in Table 2.

**Table 2 Tab2:** Assessments and used instruments with timeframe indication

Outcome(s)	Instrument(s)	T0	T1	T2	T3
Primary endpoint					
Cosmetic result	Evaluation clinical photos by panel - ‘Erasmus MC panels’ questionnaire’	x		x	x
Secondary outcome					
Cosmetic result/satisfaction with breast assessed by patient	Breast Q - preoperative module	x			
	Breast Q - postoperative module		x	x	x
Patients’ Quality of life	EORTC QLQ-C30/B23 questionnaire	x	x	x	x
	EQ-5D-5 L questionnaire	x	x	x	x
Cosmetic result BCCT.core	BCCT.core software (INESC Porto Breast Research Group)	x		x	x
Radiation-induced reaction	RTOG/EORTC			x	x
Surgical strategy performed	Performed surgery/surgeries				x
Pathological result	Data of pathology reports				x
Cost-effectiveness	Quality-Adjusted Life Year (QALY) for direct and indirect costs				x

T0 = first visit outpatient clinic, T1 = 3 months postoperative, T2 = 1 year postoperative, T3 = 3 years postoperative

#### Primary outcome

The cosmetic outcome evaluation will be performed by a 6-member, independent panel using the photographs. Each panel consist of 1) a plastic surgeon/breast cancer surgeon, 2) a general practitioner, a medical doctor, 3) a radiation oncologist, 4) a layperson and 5) a breast cancer survivor. Cosmetic outcome will be evaluated using a previously reported in-house developed questionnaire containing 11 aggregating previous recommendations [17] (see Additional file 1 A ‘Erasmus MC panels’ questionnaire’). Answers are scored on a four point Harvard cosmetic scale: 0 = ‘excellent’, 1 = ‘good’, 2 = ‘moderate’, and 3 = ‘bad’ [18].

*Secondary outcome(s).*

1) Patient reported outcome is measured by the ‘BREAST-Q’, ‘EORTC-QLQ-C30/BR23’ and ‘EQ-5D-5 L’ questionnaires (T0–3).

2) Cosmetic outcome assessed by the ‘BCCT.core software’ - INESC Porto Breast Research group [19] based on medical photographs (T0–2-3).

3) Radiation reaction scored by the ‘Radiation Therapy Oncology Group/European Organization for Research and Treatment of Cancer’ – ‘RTOG/EORTC’ (T2–3) [20].

4) Surgeries performed (T3).

5) Pathological results (T3).

6) Cost-effectiveness*;* direct costs will include the pre-operative care together with the costs for (surgical) treatment. Indirect costs will generally include adjuvant operation(s) if applicable and costs of outpatient clinic visits or hospitalisation (T4).

### Data collection and statistical analysis

#### Primary study parameter

Cosmetic outcome is calculated by obtaining the mean score for all panel members. The score per panel member is based on the mean score off the 11 scored items combined. Subsequently, the mean panel evaluation will be dichotomized by defining a mean of <1.5 as superior and a mean of >1.5 as inferior. The primary outcome is the incidence of a superior cosmetic outcome in both arms. Difference will be evaluated by using the Chi-square analysis (if normally distributed) or the non-parametric Kruskal-Wallis test (if not normally distributed).

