#### Secondary study parameters

Cosmetic result assessed by the patient (BREAST-Q), cosmetic evaluation through BCCT.core and radiation-induced reaction (RTOG/EORTC) will be analysed by comparing the intervention and control group. For normally distributed categorical data, the Chi-Square test will be used and the Kruskal Wallis test if not normally distributed. Continues variables as the Q-score will be analysed making use of the Student T-test if normally distributed or Mann-Whitney U test if not normally distributed. Pathological result will be analysed by comparing the percentages of incomplete tumour excisions and mean lumpectomy specimen size between the two study arms. The secondary study parameters will be analysed based on the intention-to-treat principle (i.e. including the patients treated with mastectomy). Surgical strategies performed will be analysed by comparing the percentages of the different types of surgery performed by using a Chi-square analysis if normally distributed or Kruskal-Wallis test if not normally distributed. Patients’ quality of life, conducted through the EORTC questionnaire/Euro-QoL and BREAST-Q questionnaires will be presented in a quantitative manner. Cost-effectiveness will be calculated by Markov modelling using ‘Quality-Adjusted Life Years’ (QALY’s).

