### Sample size

In our previously performed retrospective study the incidence of a superior cosmetic result, without intervention, was 71%. An improvement of superior cosmetic outcome to 85% was considered clinically relevant. Expected clinical relevant difference is a 14% improvement in the incidence of a superior cosmetic result as evaluated by an independent panel. The sample size calculation is based on comparing two proportions in independent groups by the Chi-Square test. With 80% power and 5% significance level we need a study population of 240 patients (120 in each arm). There is a possibility that even after randomization the patient can still undergo mastectomy instead of BCS. We expect this for less than 25% patients in each arm, therefore we aim to include 300 patients in total (150 in each arm).

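### A normality condition that cannot apply to categorical data selects the test for the primary outcome and for type of surgery

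*Protocol article*

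**What the plan says.** Under Primary study parameter, the Protocol article averages the 11 items within each panel member, averages over members, and splits the result: "a mean of <1.5 as superior and a mean of >1.5 as inferior". It continues: "The primary outcome is the incidence of a superior cosmetic outcome in both arms". The next sentence gives the test: "Difference will be evaluated by using the Chi-square analysis (if normally distributed) or the non-parametric Kruskal-Wallis test (if not normally distributed".

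Under Secondary study parameters the same rule appears twice more. It appears once in general, "For normally distributed categorical data, the Chi-Square test will be used and the Kruskal Wallis test if not normally distributed", and once for the percentages of each type of surgery, "by using a Chi-square analysis if normally distributed or Kruskal-Wallis test if not normally distributed".

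The Sample size section names a single test: "The sample size calculation is based on comparing two proportions in independent groups by the Chi-Square test".

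On timing, the abstract ties the design contrast to a "14% improvement in incidence of superior cosmetic result one year after BCS". The Primary outcome, Primary study parameter and Sample size sections name no time. Table 2 lists the primary endpoint ("Evaluation clinical photos by panel") at T0, T2 (one year) and T3 (three years).

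**The concern.** A normality check is meaningful for a continuous score. It has no meaning for a superior/inferior variable or for a list of operations. Three things follow.

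- **The rule cannot be carried out as written.** The condition always fails, so the literal instruction is always Kruskal-Wallis. The trial was sized on chi-square, so the stated analysis and the design do not match.
- **The rule invites a switch of variable.** The only quantity in the primary analysis whose normality could be checked is the undichotomized panel mean. An analyst who checks it there might run the rank test there too. That would compare score distributions, not the incidence that the plan names as its primary outcome.
- **For type of surgery the fallback is not a valid choice.** Kruskal-Wallis ranks its data. Types of operation have no stated order, so the codes assigned to them determine the p-value. This outcome deserves care because the prediction model acts by changing the advised operation.

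Two smaller gaps sit beside this: the analysis text does not repeat the one-year time point, and a mean of exactly 1.5 falls in neither class.

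**Working it through.** **1. The test behind the sample size.** Inputs from Sample size: 71% and 85%, 80% power, 5% level, chi-square, 120 per arm. The usual formula is

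n = [z(α)·√(2p̄q̄) + z(β)·√(p1q1 + p2q2)]² / d²,

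with p̄ = 0.78, 2p̄q̄ = 0.3432, p1q1 + p2q2 = 0.2059 + 0.1275 = 0.3334, and d = 0.14.

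- Two-sided: (1.960 × 0.5858 + 0.842 × 0.5774)² / 0.0196 = 136.3, so 137 per arm; 151 with continuity correction.
- One-sided: (1.645 × 0.5858 + 0.842 × 0.5774)² / 0.0196 = 107.2, so 108 per arm; 122 with continuity correction.

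Of these, only the one-sided corrected version comes close to the stated 120. The Sample size section does not state sidedness or correction, so the replacement sentence should. Whether 240 is enough is a separate question.

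**2. Chi-square against Kruskal-Wallis on the primary outcome.** For two groups and a 0/1 outcome, H = (N-1)/N × Pearson chi-square. At N = 240 the factor is 239/240 = 0.9958.

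- Example near the design rates, 85/120 against 102/120: pooled proportion 187/240 = 0.7792; chi-square = (17/120)² / (0.7792 × 0.2208 × 2/120) = 7.00, p = 0.0082. H = 0.9958 × 7.00 = 6.97, p = 0.0083.
- Borderline example, 85/120 against 98/120: chi-square 3.888, p = 0.0486; H = 3.872, p = 0.0491.
- Exact binomial enumeration at 120 per arm, two-sided 5%: type I error at 71% in both arms is 5.00% for either test, and power at 71% against 85% is 75.5% for either. The probability that the two tests reach different decisions is below one in a million.

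On the outcome as defined, the choice of test has practically no effect on the primary result.

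**3. Type of surgery.** The Prediction model section names primary BCS, oncoplastic BCS, and mastectomy with or without reconstruction. Taken as four categories, with **invented** counts of 150 per arm:

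| | A | B | C | D |
|---|---|---|---|---|
| Control | 110 | 15 | 15 | 10 |
| Intervention | 100 | 30 | 8 | 12 |

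- Chi-square: the expected counts per arm are 105, 22.5, 11.5 and 11. The statistic is 2 × (25/105 + 56.25/22.5 + 12.25/11.5 + 1/11) = 7.79 on 3 df, p = 0.051. It is the same for any labelling.
- Kruskal-Wallis over all 24 codings (12 distinct results, since reversing an order changes nothing): the smallest p is 0.007 (order C, A, D, B), the largest 0.65 (order D, A, B, C), and the order as tabulated gives 0.34. Eight of the 24 codings fall below 0.05.

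**4. The exact tie.** Six members × 11 items = 66 scores, and 66 × 1.5 = 99, a whole number, so a mean of exactly 1.5 can occur. The Primary outcome section numbers only five roles. With five members and complete scoring the sum would have to be 55 × 1.5 = 82.5, and no tie could occur.

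**The case against.** The strongest defence is that the primary result is safe. The sentence on the difference directly follows the definition of the incidence, so its plain reading is a test on the dichotomized outcome, where the two tests coincide. That stands, and it limits the finding on the primary endpoint to wrong wording and a mismatch with the Sample size section.

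A reader might infer more, and the document does not support it:

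- **An inflated type I error from the choice of test.** On the binary outcome both tests hold 5.00%. Even if a normality check on the panel score decided between chi-square on the dichotomy and Kruskal-Wallis on the score, following the rule does not inflate the error. Simulation of that reading under the null (6,000 trials per setting, normal and mildly skewed scores, 112 and 150 per arm) gave 4.5-5.1%. Inflation needs picking the better result afterwards, which no section permits.
- **An open time point.** If significance at either one or three years counted as success, the error would be 7.8-9.1% at assumed correlations of 0.8 to 0.5. No section says that either would count. The abstract ties the powered contrast to one year. Table 2 is a collection schedule that also marks T0, before surgery, so a mark there does not declare an analysis time.
- **An open cut-off.** The cut-off is fixed at 1.5; only the exact value is unassigned.

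For type of surgery, one can say that the outcome is secondary, that the plan compares percentages, and that the table above is invented. All true. The table shows only that the p-value can depend on the coding, not how far it would in this trial. One might also order operations by extent, but the article states no such order.

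**Conclusion.** The point holds as an error in a stated rule, not as a threat to the primary result. The normality condition cannot apply to the categorical outcomes it governs, and it contradicts the chi-square basis of the sample size.

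- **Primary outcome:** negligible effect on the p-value (0.0082 against 0.0083 near the design rates), provided the test is applied to the superior/inferior variable. The answer could differ only if the fallback were applied to the undichotomized score, which the article does not say.
- **Type of surgery:** a real defect. Kruskal-Wallis gives a p-value that depends on an arbitrary coding. The range 0.007 to 0.65 illustrates the mechanism and rests on assumed counts.
- **Time point and tie:** clarifications only.

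Confidence is high on the wording and on the identity between the two tests. The normality rule for continuous scores (t-test or Mann-Whitney) is not part of this point.

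**What to change.** - Delete the normality conditions wherever the outcome is binary or categorical, in both analysis sections.
- Primary: one two-sided chi-square test on superior/inferior at one year (T2), reported with the difference in proportions and its 95% CI. State whether a continuity correction is used. Label the three-year (T3) comparison as secondary.
- Type of surgery: always chi-square or, with sparse cells, Fisher's exact test.
- Other categorical outcomes: name one test for each in advance. Which test to use for ordered grades is a matter of preference for the trial team.
- Assign a mean of exactly 1.5 to one class, for example inferior as 1.5 or above.

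The cost is a few sentences in the protocol or analysis plan, with no extra data or patients. The change is best made before outcome data are examined.

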#### Secondary study parameters

Cosmetic result assessed by the patient (BREAST-Q), cosmetic evaluation through BCCT.core and radiation-induced reaction (RTOG/EORTC) will be analysed by comparing the intervention and control group. For normally distributed categorical data, the Chi-Square test will be used and the Kruskal Wallis test if not normally distributed. Continues variables as the Q-score will be analysed making use of the Student T-test if normally distributed or Mann-Whitney U test if not normally distributed. Pathological result will be analysed by comparing the percentages of incomplete tumour excisions and mean lumpectomy specimen size between the two study arms. The secondary study parameters will be analysed based on the intention-to-treat principle (i.e. including the patients treated with mastectomy). Surgical strategies performed will be analysed by comparing the percentages of the different types of surgery performed by using a Chi-square analysis if normally distributed or Kruskal-Wallis test if not normally distributed. Patients’ quality of life, conducted through the EORTC questionnaire/Euro-QoL and BREAST-Q questionnaires will be presented in a quantitative manner. Cost-effectiveness will be calculated by Markov modelling using ‘Quality-Adjusted Life Years’ (QALY’s).

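### The stated comparison of patient-reported scores does not use the T0 questionnaires, and the wording for EORTC and EQ-5D does not clearly commit to a between-arm estimate

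*Protocol article*

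**What the plan says.** **Analysis.** The Secondary study parameters section lists BREAST-Q among the outcomes compared between the two arms, and then gives the test: "Continues variables as the Q-score will be analysed making use of the Student T-test if normally distributed", with a Mann-Whitney U test otherwise. It names no baseline covariate, change score, repeated-measures model or time point. Later in the same section, quality of life from the EORTC, Euro-QoL and BREAST-Q forms appears again, this time with the statement that these "questionnaires will be presented in a quantitative manner". Secondary outcomes are to be analysed by intention to treat.

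**Data collected.** Under Pre-operative work-up: "Preoperatively all patients will be asked to complete three questionnaires". Under Follow-up: "Follow-up visits will be scheduled at 3 months (T1), 1 year (T2), and 3 year (T3) postoperatively", with the questionnaires repeated each time. Table 2 marks EORTC and EQ-5D-5L at T0, T1, T2 and T3. For BREAST-Q it lists "Breast Q - preoperative module" at T0 and the postoperative module at T1 to T3.

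**Purpose.** The hypothesis in the Objective is that the prediction model "improves cosmetic outcome and quality of life in patients opting for BCS".

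**The concern.** Two things in this section are weaker than the data allow.

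First, the test named for the BREAST-Q score leaves out a measurement that every patient is asked to give. A T0 score that correlates with the follow-up score explains part of the spread between patients. If it is left out, that spread stays in the standard error and the confidence interval is wider than it need be. The Discussion presents preoperative collection of these outcomes as a strength, yet no between-arm analysis in the article uses them.

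Second, the wording for EORTC and EQ-5D can be read as description by arm or as a comparison. The same section is explicit about comparing arms for type of surgery, pathology, BCCT.core and radiation reaction. For quality of life, which the hypothesis names, the reader cannot tell what estimate will be reported. BREAST-Q falls under both sentences, so the two need reconciling in any case.

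At stake is the precision and clarity of secondary results, not the validity of the trial.

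**Working it through.** **Figure to reproduce.** The article gives no sample size, power, standard deviation or target difference for any patient-reported score. Its sample size rests on the panel-rated primary endpoint alone. It is used here only for the planned number of patients.

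**Inputs**
- Patients per arm: 150 (Sample size), all analysed by intention to treat (Secondary study parameters). Complete questionnaires are assumed.
- Two-sided 5% level and 80% power: assumed for this illustration, giving 1.960 + 0.8416 = 2.8016.
- Correlation r between T0 and follow-up score: not in the article. Assumed 0.3 to 0.7, with 0.2 added as a low case.
- Differences are in SD units because no SD is given.

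**Step 1. Unadjusted t-test.** Detectable difference = 2.8016 × √(2/150) = 2.8016 × 0.1155 = 0.323 SD.

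**Step 2. Adjustment for T0 (ANCOVA).** The variance of the treatment difference is multiplied by 1 − r². Hence:
- equivalent unadjusted size = 150/(1 − r²) per arm
- detectable difference = 0.323 × √(1 − r²)
- power at 0.323 SD = Φ(2.8016/√(1 − r²) − 1.960)

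| r (assumed) | 1 − r² | Equivalent unadjusted n per arm | Gain in patients | Detectable difference (SD) | Power at 0.323 SD |
|---|---|---|---|---|---|
| no adjustment | 1 | 150 | none | 0.323 | 80% |
| 0.2 | 0.96 | 156 | 4% | 0.317 | 81.6% |
| 0.3 | 0.91 | 165 | 10% | 0.309 | 83.6% |
| 0.5 | 0.75 | 200 | 33% | 0.280 | 89.9% |
| 0.7 | 0.51 | 294 | 96% | 0.231 | 97.5% |

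The interval width shrinks by 1 − √(1 − r²): about 5%, 13% and 29% at r = 0.3, 0.5 and 0.7.

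**Step 3. Check by simulation.** With 150 per arm, a true difference of 0.323 SD and 4,000 simulated trials per correlation, power for the t-test against ANCOVA was 78.8% and 83.2% (r = 0.3), 81.1% and 89.9% (r = 0.5), and 78.7% and 97.8% (r = 0.7). This agrees with the formula.

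**Step 4. Fewer questionnaires returned.** With 120 per arm the detectable difference is 2.8016 × √(2/120) = 0.362 SD unadjusted, and 0.345, 0.313 and 0.258 SD at r = 0.3, 0.5 and 0.7. The absolute values move, but the relative gain does not.

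**Step 5. Would a t-test on change scores do as well?** The text does not say that change is analysed. If it were, the variance relative to the unadjusted test would be 2(1 − r): 1.4, 1.0 and 0.6 at r = 0.3, 0.5 and 0.7, against 0.91, 0.75 and 0.51 for ANCOVA. Change would therefore be worse than ignoring T0 at r = 0.3 and no better at r = 0.5. For BREAST-Q, subtracting a preoperative-module score from a postoperative-module score is doubtful anyway. A covariate need not share the outcome's scale.

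**The case against.** **The t-test is valid.** This stands. Under 1:1 randomisation the unadjusted comparison is unbiased with correct type I error, and chance imbalance at T0 is already covered by its confidence interval. A reader might infer that leaving out T0 biases the result. It does not; the loss is one of precision.

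**The quality-of-life wording need not mean description only.** This also stands. BREAST-Q is in the sentence about presentation, yet the same section says it is compared between arms. The t-test sentence can also be read as covering continuous scores in general, with the Q-score as an example. A reader might infer that the plan makes no quality-of-life comparison and so cannot answer that part of its hypothesis. The text is too vague to support that. It supports only that a between-arm estimate is not clearly promised.

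**Quality of life is secondary.** This stands too. The stated aim and the comparison in the Objective concern cosmetic outcome, and only that endpoint is powered. Calling quality of life half of the hypothesis would give it more weight than the article does.

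**The size of the gain is assumed.** Correct. The article gives no correlation, T0 is the first outpatient visit after a cancer diagnosis, and at r = 0.2 the gain is only 4%. BREAST-Q, the one instrument named with the t-test, is also the one whose T0 form differs, so its correlation may be lower. EORTC and EQ-5D use the same instrument throughout.

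**The detail may be in the SAP.** It may, and then the article is merely abridged. But the article does name a test, and the point concerns that stated method.

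**Conclusion.** The point holds as a matter of precision and clarity. The method stated for the BREAST-Q score makes no named use of T0, and the wording for EORTC and EQ-5D does not clearly commit to an estimated difference, although the hypothesis includes a quality-of-life benefit.

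Adjusting for T0 would be worth about 10% to 96% more patients for correlations of 0.3 to 0.7, and about 33% at 0.5. That range is an assumption, and the value for BREAST-Q may lie towards or below its lower end. The detectable differences assume 150 per arm with complete data. The figures compare ANCOVA with the t-test; no equivalent was computed for the Mann-Whitney test.

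Nothing here makes the planned test invalid or touches the primary endpoint.

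**What to change.** For each BREAST-Q, EORTC and EQ-5D scale to be reported, replace the unadjusted test and the wording about presentation with one statement: a between-arm difference with 95% confidence interval, from ANCOVA or from a repeated-measures model over T1 to T3, with the T0 score as covariate, under the intention-to-treat principle already stated. State the time point to which the main estimate refers.

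Three details should be settled in the same wording:
- **Timing of T0.** Table 2 puts T0 at the first outpatient visit, but Pre-operative work-up does not say whether the forms are completed before the treatment advice is discussed. Use as covariate only T0 questionnaires completed before that advice can have had an effect.
- **Missing or late T0.** A patient without a usable T0 score should stay in the analysis. Say how the missing covariate is handled.
- **BREAST-Q modules.** Name the preoperative score that serves as covariate for each postoperative scale, and do not analyse change between modules unless their scores are comparable.

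The cost is wording only. No new data, visits or patients are needed, and the outcomes remain secondary.
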